**Fig. 2 Fig2:**
[figure not shown]
Stepped-wedge design of the MOHMQuit trial

The stepped-wedge cluster-randomised controlled trial design was chosen because the intervention is at the service level and this design is recommended as a “pragmatic randomised study design… for the evaluation of service delivery outcomes” ([49], p6). Additionally, a stepped-wedge design is more powerful than a parallel cluster design in situations where there are relatively small numbers of eligible services; and it allows sites to act as their own historical controls, while also allowing observation of any within site temporal trends [49, 51]. While it is possible to offer the intervention to control sites at the end of a parallel cluster design trial, there are rarely sufficient time or resources remaining to provide this effectively and ethically. Additionally, the level of evidence provided by a stepped-wedge design is considered to be robust and comparable with other cluster randomised controlled trial designs [48, 49].

To prepare the MOHMQuit study protocol paper we have followed the Consolidated Standards of Reporting Trials (CONSORT) extension for the stepped wedge cluster randomised trial [50] (Additional file 3) and where applicable, the TIDieR (Template for Intervention Description and Replication) Checklist [52] (Additional file 4).

### Participants

#### Eligibility criteria—study sites

To be eligible for participation, maternity services were required to provide antenatal care and birthing services and to also (i) have a prevalence of smoking in the first half of pregnancy ≥ 12%; and (ii) have a minimum of 80 women smoking in the first half of pregnancy per year [53]. These criteria ensured that the intervention will be offered in services with smoking prevalence higher than the Australian average of 9.5% in the first half of pregnancy [11]; and provide an adequate number of smokers at each site. All antenatal services providing care to women intending to give birth at these sites were eligible to participate, including hospital-based, community-based and outreach services. Nine eligible maternity services have confirmed participation.

#### Eligibility: participants—maternity service leaders and clinicians

The following clinicians working in public maternity care services at participating sites will be eligible to participate:*Maternity service leaders (leaders):* all maternity service leaders who support or supervise clinicians providing antenatal care at each site, its catchment, and associated services, will be eligible (see Table 1).*Maternity care clinicians (clinicians):* all clinicians providing antenatal care, including midwives, obstetricians, obstetric trainees, and Aboriginal health workers, will be eligible to participate (see Table 1).

#### Eligibility: participants—pregnant and postpartum women

Pregnant/postpartum women who meet all the criteria below will be eligible to participate:Received antenatal care through participating maternity services (including community based and outreach services and the Aboriginal Maternal and Infant Health Service [44])Birthed their baby at one of the participating services during the study periodIndicated that they were smokers or quit during this pregnancy at their first antenatal appointment with a health care practitioner at the participating maternity services, as recorded in eMaternity. (Smoking status is a required field in eMaternity at this initial visit).

Pregnant women receiving *antenatal* care at participating sites will be excluded from the study if:They indicate they wish to opt-out from the studyThey experience a perinatal death in this pregnancy or birthTheir baby is transferred to a Neonatal Intensive Care UnitThey do not speak EnglishThey are less than 16 years of age at the time of data collectionA Research Midwife assesses that they are unable to provide informed consent

### Recruitment and consent

#### Services

Prior to the submission of the trial funding application, maternity services across NSW meeting these criteria were approached to explore interest in participation*—*9 of 15 services approached agreed to participate and contributed to the funding application.

#### Staff (maternity service leaders and clinicians)

##### Maternity service leaders

The study will be promoted by the Midwifery Partner Investigators at each site. While each site has already agreed to participate in the trial, individual maternity service leaders and clinicians will still be provided with a Participant Information Statement (PIS) and asked to provide individual consent to participate in data collection processes. They will be invited to participate by their manager and be provided with detailed information about the study. Written consent to participate will be sought at the leaders’ workshop.

##### Maternity care clinicians

All clinicians providing antenatal care will be informed of the trial by their manager or other service leaders, provided with detailed information and invited to participate in the trial and provide consent to the data collection processes. This process is consistent with usual practice in health services and with our pragmatic study design.

#### Pregnant and postpartum women

A two-stage recruitment and consent process will be used to recruit pregnant and postpartum women to the study. In an initial opt-out process, all pregnant women presenting for antenatal care at the services will receive a PIS and be given the option of opting out of the study by contacting a research midwife by text. For women who remain and meet the eligibility criteria, a research midwife will contact them by text and then a telephone call, give a verbal explanation of the study, encourage women to ask any questions, and ask women to provide verbal consent to participating in a brief telephone interview. Women who consent to the telephone interview, and who report smoking abstinence in the 7 days before the birth of their baby, and since giving birth, will also be asked to consent to giving a saliva sample for cotinine testing. Importantly, all women will receive full ante- and postpartum care regardless of whether they consent to participate in the study.

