**Primary health outcome**				
Biochemically verified 7-day point prevalence abstinence at the end of pregnancy among pregnant smokers and recent quitters, confirmed by salivary cotinine testing. (Aim 1)	Structured telephone interview^a^ and salivary cotinine testing	Postpartum women	Within 2 weeks after giving birth	• The primary analysis will compare the odds of quitting smoking (cotinine-confirmed 7-day point prevalence abstinence) after the adoption of the intervention relative to the baseline rate. • To achieve this, logistic regression will be used within a generalised linear mixed model framework. • In addition to the fixed effect for intervention, a fixed effect for time will be included to adjust for any secular trends in the outcome. Random effects for site and time within site will be included to account for clustering by site and repeated measures over time. • Women who do not complete the biochemical verification will be classified as continuing smokers, as recommended in analyses of smoking cessation trials (e.g., see [56]).

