**Intervention outcomes**				
Documented provision of smoking cessation support (SCS) at booking visit and any subsequent visits. Offer of: • referral to a smoking cessation service including NSW Quitline • behavioural support • nicotine replacement therapy (Aim 2)	Deidentified data extraction of specified variables for all births to eligible women at intervention sites	*e*Maternity^b^	Throughout the 32-month collection period	• *e*Maternity SCS scores will be calculated based on the documented provision of SCS in *e*Maternity for each woman at each visit. • Scores will be modelled using a linear mixed model. Fixed effects will be included for time, intervention, and the interaction of these. •Random effects for site and participant will be included to account for clustering by site, and repeated measures on participants. •The interaction term will directly compare the rate of change in SCS scores over antenatal visits between pre and post-intervention.
Self-reported: • Provision of Advice to quit smoking • Provision of Assistance to quit smoking • Provision of referral to a quit smoking service (e.g. NSW Quitline or local service). (Aim 3)	Study specific questionnaire	Clinicians	Before training and 6 months post-training	• The outcome measure will be a composite score of self-reported provision of SCS, calculated from the questionnaires completed by clinicians prior to training and at 6 months post-training. • Post-intervention clinician SCS scores will be modelled using a linear mixed model. Fixed effects will be included in the model for the pre-intervention SCS score and time. A random effect will be included for site to account for randomisation by cluster.
Women’s reported receipt of: • Advice on quitting • Referral to a quitting program • Written self-help materials (Aim 5)	Structured telephone interview^a^	Postpartum women	Within 2 weeks after giving birth	• Receipt of SCS reported by women will be modelled using logistic regression in a generalised linear mixed model framework. Fixed effects for time and intervention will be included in the model and a random effect for site will be used to account for randomisation by cluster.
**Mediators** (for more detail on the identified barrier, intervention types, behaviour change techniques and measures, see Additional file 1)				

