**Economic evaluation**				
Cost-effectiveness—the incremental cost per additional quitter from a service-provider perspective (Aim 6)	Within-trial data collection	Data will be sourced from study and site records as well as the existing literature.	Data collection throughout the study, with analysis at the end.	Economic evaluation conducted from the perspective of the Australian health care system with 8-month time horizon for cost-effectiveness and lifetime time horizon for cost utility. Probabilistic sensitivity analysis and non-parametric bootstrapping will be used to assess robustness of the model.
Cost-utility—lifetime analysis of the incremental cost per Quality adjusted life year (QALY) gained (Aim 6)	Modelled economic evaluation	Data will be sourced from study and site records as well as the existing literature.	Data collection throughout the study, with analysis at the end.	

*Key: NSW* New South Wales, *NSW Quitline* A state-based telephone Quitline service, *SCS* smoking cessation support, *eMaternity* the electronic health record used by maternity services in NSW.

^a^Study specific interview with postpartum women: women will be interviewed by a research midwife by telephone within 2 weeks of giving birth and asked about their smoking status in the final 7 days of their pregnancy. They will also be asked their perspectives of SCS provided in antenatal care using a structured interview schedule.

^b^Data extractions from eMaternity: deidentified, quantitative data will be extracted from the eMaternity database throughout the 32-month data collection period to analyse clinicians’ provision of best-practice SCS as documented in electronic-medical records (aim 2).

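### Women consent to the outcome interview after exposure, and the stated primary model omits booking smoking status, so a change in participant mix at a site's switch would be counted as intervention effect

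*Protocol article*

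**What the plan says.** **Consent.** Under Recruitment and consent (Pregnant and postpartum women), there are two stages. The first is antenatal: "In an initial opt-out process, all pregnant women presenting for antenatal care at the services will receive a PIS", with the option to opt out. In the second, a research midwife contacts the women who remain and are eligible, to "ask women to provide verbal consent to participating in a brief telephone interview". Eligibility requires having given birth at a participating service, and a footnote to Table 2 says that "women will be interviewed by a research midwife by telephone within 2 weeks of giving birth".

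**Population.** The eligibility section admits women recorded in eMaternity as "smokers or quit during this pregnancy at their first antenatal appointment". Smoking status is a required field at that visit. The primary outcome row of Table 2 likewise covers both smokers and recent quitters.

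**Primary model.** Table 2 specifies logistic regression in a generalised linear mixed model: "In addition to the fixed effect for intervention, a fixed effect for time will be included". It adds: "Random effects for site and time within site will be included to account for clustering by site and repeated measures over time". No characteristic of the woman is named. Women without biochemical verification count as smokers. Nothing is said about eligible women who decline the interview or cannot be reached.

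**Other data.** For Aim 2, Table 2 plans "Deidentified data extraction of specified variables for all births to eligible women at intervention sites".

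**The concern.** The step that decides who supplies outcome data comes after the woman's care under usual practice or MOHMQuit. That care may influence her willingness to talk about smoking, and the influence may differ between women who have quit and women who have not.

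The two booking groups can be expected to differ widely in their chance of abstinence at the end of pregnancy, so the overall rate depends on their proportions among participants. If those proportions change when a site switches, the change is aligned with the intervention term. The time effect is there for secular trends ("a fixed effect for time will be included to adjust for any secular trends in the outcome"), and the random effects describe variation between and within sites. Neither removes a change that coincides with the switch. Cotinine testing guards against misreporting, not against a change in who takes part.

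At stake is the primary estimate, for which the planned effect is 5 percentage points (16% to 21%).

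**Working it through.** **Inputs from the article.** Baseline abstinence 16%, target 21%, ICC 0.02, cluster autocorrelation 0.7, nine sites, 40 consenting women per site per two months, 32 months. The planned total reproduces: 9 × 40 × 12 = 4320. It counts women who consent, so it gives no participation rate.

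**Inputs assumed.** All participation rates, group shares and group-specific abstinence rates below. The article gives none of them.

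**(a) Shift in booking-status mix, no true effect.** Crude rate = s × a + (1 − s) × c, where s is the already-quit share and a and c are abstinence in already-quit women and current smokers. Take a = 60% and c = 5%.
- s = 20%: 0.20 × 0.60 + 0.80 × 0.05 = 16.0%
- s = 25%: 0.25 × 0.60 + 0.75 × 0.05 = 18.75% (+2.75 points)
- s = 30%: 0.30 × 0.60 + 0.70 × 0.05 = 21.5% (+5.5 points)
- s = 15%: 0.15 × 0.60 + 0.85 × 0.05 = 13.25% (−2.75 points)

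The change is the shift in share times the gap a − c, here 0.05 × 0.55 = 0.0275. A smaller gap gives less. With a = 44% and c = 9% (again 16.0% at s = 20%), the 5-point shift gives 0.05 × 0.35 = 1.75 points. Within each booking group the rates are the same in both phases, so a model with booking status would find no effect.

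**(b) Selection on final smoking status, no true effect.** Let r be the post/pre change in the ratio of abstainers' to smokers' participation. Observed rate = 0.16r / (0.16r + 0.84).
- r = 1.1: 17.3%
- r = 1.2: 0.192 / 1.032 = 18.6%
- r = 1.4: 0.224 / 1.064 = 21.1%
- r = 1/1.2: 13.7%

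The whole planned effect appears at r = (0.21/0.79) / (0.16/0.84) = 1.396. In the other direction, a true rise to 21% with r = 1/1.2 is observed as 0.175 / (0.175 + 0.79) = 18.1%.

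**Does the stated model structure absorb it?** A simulation with no true effect used nine sites, 16 two-month periods, four periods excluded per site, 40 women per cell, ICC 0.02 and autocorrelation 0.7. It was analysed by a linear (generalised least squares) analogue with intervention, period, site and site-by-period terms. The layout is assumed because Fig. 2 is not shown.

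| Participation pattern | Mean intervention estimate |
|---|---|
| No shift | 0.0 points |
| r = 1.2 after each site's switch | about +2.5 points |
| r = 1.4 after each site's switch | about +4.9 points |
| Calendar drift common to all sites, r from 1 to 1.4 | about +0.1 point |

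**What booking status can and cannot correct.** In (b), r multiplies the odds of abstinence in every booking group. With r = 1.2 and the groups from (a):
- already quit: 0.72 / (0.72 + 0.40) = 64.3%, against 60%
- current smokers: 0.06 / (0.06 + 0.95) = 5.9%, against 5%

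The odds ratio within each group is still 1.2. Weighting to the true 20/80 mix gives 0.20 × 64.3% + 0.80 × 5.9% = 17.6%, so 1.6 of the 2.6 spurious points remain.

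**Alternative denominator.** If all eligible women were analysed and non-participants counted as smokers, a rise in participation from 60% to 70% alone would move 16% to 16% × 70/60 = 18.7%. The problem does not depend on the denominator chosen.

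**The case against.** **Detail for the SAP.** This is a journal article, and covariates and sensitivity analyses are often left to a SAP, which is not shown. This stands in part: an unseen SAP may already contain the adjustment. But the article itself fixes the late consent and lists the primary model's terms, so adding a covariate is a change to what is stated.

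**Existing protections.** Randomisation and blinding states that women, interviewing midwives and analysts are blinded to phase. Data are collected independently of the sites, and the opt-out stage is antenatal. These limit selection driven by the recruiter. They do not govern a woman's own decision after the care she received.

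**Direction.** A reader might infer that the bias favours the intervention, because women who have quit would be readier to talk. The documents do not support this: they give no participation rate by phase or smoking status. The workshops include reframing smoking, and better support could equally make continuing smokers more willing to take part, which would dilute a true effect.

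**Adjustment.** A reader might also infer that the model adjusts for nothing but time, or that adding booking status would cure the problem. Neither is right. The model has random effects for site and time within site, and the last part of the (b) calculation shows what adjustment leaves behind.

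**Population.** The Primary hypothesis section refers only to women reporting current smoking at booking. Under that population the booking-mix mechanism disappears. The eligibility section and Table 2 include recent quitters, however, and the primary analysis is described for that wider group.

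**The covariate itself.** After a site switches, trained staff elicit booking status, so its recording could change with phase. This stands as a caveat.

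**Conclusion.** The point holds as a limited one. Consent to the outcome interview follows exposure, the sample mixes two groups with different prospects, and the stated model has no term for the group. A change in participant mix tied to each site's switch would be counted as intervention effect, whereas drift common to all sites would be largely absorbed.

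The size and direction in this trial are unknown. Under the assumed rates, a 5-point shift in the already-quit share moves the crude rate by 1.75 to 2.75 points either way, against a planned effect of 5 points. These figures show what a shift would do, not that one will occur. The simulated pass-through also rests on an assumed layout. The change is worth making because the variable defines eligibility and is therefore known for every participant.

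**What to change.** 1. Add booking smoking status from eMaternity (current smoker or already quit) as a fixed covariate in the primary model.
2. Prespecify a sensitivity analysis that weights participants to all eligible women by site, period and booking status. Aggregate eMaternity counts suffice, so no record linkage is needed. Confirm first that booking status is among the variables to be extracted; the article describes the extract only for documented support under Aim 2.
3. Report participation by phase and booking status beside the primary result.
4. State the limit: adjustment and weighting correct a shift in booking-status mix, and the covariate adds precision. Neither removes selection on final smoking status within a booking group. For that, participation by phase is only a warning signal.

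**Cost.** One covariate, one weighted analysis and one table. The odds ratio becomes conditional on booking status, the weighted intervals will be somewhat wider, and the report must note that trained staff elicit booking status after the switch.

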### Data collection and analysis

Mixed methods evaluation of the intervention and its implementation will be undertaken. Mixed methods evaluations are recommended as being practical and suitable for implementation research [54, 55]. Using a mixed methods evaluation will enable the multiple perspectives of leaders, clinicians and pregnant women to be understood, while examining multiple types of outcomes [54].

Data on the intervention and health outcomes and the implementation process will be collected by the research team, independently from each site. Variables to be collected, with the method of collection and source, timepoint of measurement and methods of analysis are shown in Table 2. Information on the types of data collected from each source are also illustrated in Fig. 3. An explanation of the relationship between the identified barriers, intervention types, behaviour change techniques and measures for the mediators are shown in Additional file 1. Analysis for aim 8 (examining the mechanisms of action of the intervention strategies and moderators of their impact) which assesses the interactions between many of the variables, is provided below Table 2. More detail regarding the process evaluation and the economic evaluation will be provided in separate protocol papers.

**Table 2 Tab2:** MOHMQuit data collection and analysis

Measure	Methods of data collection	Source	Timepoint	Data analysis
**Primary health outcome**				
Biochemically verified 7-day point prevalence abstinence at the end of pregnancy among pregnant smokers and recent quitters, confirmed by salivary cotinine testing. (Aim 1)	Structured telephone interview^a^ and salivary cotinine testing	Postpartum women	Within 2 weeks after giving birth	• The primary analysis will compare the odds of quitting smoking (cotinine-confirmed 7-day point prevalence abstinence) after the adoption of the intervention relative to the baseline rate. • To achieve this, logistic regression will be used within a generalised linear mixed model framework. • In addition to the fixed effect for intervention, a fixed effect for time will be included to adjust for any secular trends in the outcome. Random effects for site and time within site will be included to account for clustering by site and repeated measures over time. • Women who do not complete the biochemical verification will be classified as continuing smokers, as recommended in analyses of smoking cessation trials (e.g., see [56]).

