**Methods:**

A stepped-wedge cluster-randomised design will be used. Implementation of MOHMQuit will include reinforcing leadership investment in SCS as a clinical priority, strengthening maternity care clinicians’ knowledge, skills, confidence and attitudes towards the provision of SCS, and clinicians’ documentation of guideline-recommended SCS provided during antenatal care. Approximately, 4000 women who report smoking during pregnancy will be recruited across nine sites. The intervention and its implementation will be evaluated using a mixed methods approach. The primary outcome will be 7-day point prevalence abstinence at the end of pregnancy, among pregnant smokers, verified by salivary cotinine testing. Continuous data collection from electronic medical records and telephone interviews with postpartum women will occur throughout 32 months of the trial to assess changes in cessation rates reported by women, and SCS documented by clinicians and reported by women. Data collection to assess changes in clinicians’ knowledge, skills, confidence and attitudes will occur prior to and immediately after the intervention at each site, and again 6 months later. Questionnaires at 3 months following the intervention, and semi-structured interviews at 6 months with maternity service leaders will explore leaders’ perceptions of acceptability, adoption, appropriateness, feasibility, adaptations and fidelity of delivery of the MOHMQuit intervention. Structural equation modelling will examine causal linkages between the strategies, mediators and outcomes. Cost-effectiveness analyses will also be undertaken.

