### Primary hypothesis

Among pregnant smokers (women reporting current smoking at antenatal booking) there will be a 5% increase in cotinine-confirmed 7-day point prevalence abstinence from a baseline prevalence of 16%, after introduction of MOHMQuit. This conservative estimate is based on the effectiveness of antenatal psychosocial smoking cessation interventions in the latest Cochrane review (RR 1.44, 95%CI 1.19-1.73) [17].

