### Sample size

The trial aims to recruit 4320 pregnant women who smoke over the 32 months of data collection across the nine sites.

NSW Health data indicate there were over 2000 women smoking in the first half of pregnancy in the participating sites in 2018. Assuming that at each of the 9 sites on average 40 participants will consent every 2 months, the total sample size available will be 9 × 40 × 12 = 4320. Using a significance level of 5% and assuming an intra cluster correlation (ICC) of 0.02 and a cluster autocorrelation of 0.7, the primary analysis will have more than 80% power to detect an increase in 7-day point prevalence abstinence of 5% from a baseline prevalence of 16% (i.e. intervention 21% vs control 16%). This conservative estimate is based on the effectiveness of antenatal psychosocial smoking cessation interventions in the latest Cochrane review (RR 1.44, 95%CI 1.19–1.73) [17].

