### Advantages of the pragmatic stepped wedge trial design

The MOHMQuit trial has been designed as a pragmatic trial according to the PRECIS-2 criteria [64]. The stepped-wedge cluster-randomised design is a pragmatic study design commonly used in the evaluation of service delivery interventions [50]. Policy makers need strong evidence of effectiveness and cost-effectiveness in ‘real world’ conditions [65]. A strength of this design is that it focuses on carrying out ‘real-world’ research, which in this case is representative of genuine clinical practice in the provision of maternity care in public antenatal services with a range of different models of care [66]. This trial will also provide evidence of the practicality of using the MOHMQuit intervention in the provision of ‘real world’ maternity care provided by usual antenatal care providers, with all pregnant women who smoke or quit smoking since becoming pregnant being eligible to participate [66].

The stepped-wedge design has several advantages for translational research, including that (a) it controls for between-service variation in baseline practice; (b) statistical power is boosted as it allows assessment of intervention effects in a pre-/post-comparison across services; and (c) assessment of sustainability can occur in services that transition earlier [67]. The design is particularly suited to implementation trials of service delivery interventions as it ensures all sites receive the intervention, while allowing assessment of whether (a) a change in quit rates has occurred; (b) the change is likely due to the intervention; and (c) the change is significant [49]. The 32-month timeframe of the MOHMQuit trial facilitates measurement of the success of the intervention over a long period, also enabling the sustainability of the intervention to be assessed. Finally, the stepped-wedge design also allowed for flexibility in adapting the design of the study in response to delays resulting from the impact of COVID-19 on the health care system and redesign work being completed in *e*Maternity.

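### The primary hypothesis and power are for women smoking at booking, but the primary outcome also includes women who had already quit, so the 16% versus 21% basis does not describe the population analysed

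*Protocol article*

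**What the plan says.** Three places in the protocol article describe smokers only. The Primary hypothesis reads "Among pregnant smokers (women reporting current smoking at antenatal booking) there will be a 5% increase in cotinine-confirmed 7-day point prevalence abstinence", and the sentence continues "from a baseline prevalence of 16%, after introduction of MOHMQuit". The Sample size section says "The trial aims to recruit 4320 pregnant women who smoke over the 32 months of data collection across the nine sites" and gives more than 80% power for 21% against 16%. The abstract gives the primary outcome as "7-day point prevalence abstinence at the end of pregnancy, among pregnant smokers, verified by salivary cotinine testing".

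Four places describe a wider group. The eligibility criteria for pregnant and postpartum women admit those recorded in eMaternity at their first visit either as smokers or as having quit during this pregnancy. Table 2 sets the primary outcome as "Biochemically verified 7-day point prevalence abstinence at the end of pregnancy among pregnant smokers and recent quitters, confirmed by salivary cotinine testing", and the secondary self-report outcome names the same two groups. The Discussion, under the advantages of the pragmatic design, describes the trial as one "with all pregnant women who smoke or quit smoking since becoming pregnant being eligible to participate".

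No expected share, baseline rate or effect is given for recent quitters. The primary model in Table 2 lists fixed effects for intervention and time and random effects for site and time within site.

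**The concern.** This is more than loose wording. The hypothesis restricts explicitly to current smoking at booking, and Table 2 names recent quitters as a second group. The two definitions give different analysis sets and answer different questions: one is about cessation among smokers, the other mixes cessation with the prevention of relapse.

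A woman who has stopped before her first visit starts out abstinent. Unless her chance of verified abstinence at the end of pregnancy is no better than 16%, including her raises the baseline rate and with it the binomial variance. If the intervention mainly helps smokers to stop, including her also shrinks the pooled difference. The stated 16%, 21% and power therefore cannot be carried over to the outcome as Table 2 defines it. While both definitions stand, the choice between them could also be made after the data are seen.

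**Working it through.** **The plan's own figures.** The recruitment total reproduces: 9 sites × 40 women × 12 two-month periods = 4320. The rates are 16% and 21%, a difference of 5 points. The mean is 18.5%, so the binomial variance is 0.185 × 0.815 = 0.151. The power claim is taken as given; the figure showing the layout is not available, and this point does not depend on rebuilding it.

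**Assumed inputs, not in the article.** Let q be the share of recent quitters among recruits and a their verified abstinence under usual care. Three scenarios are used: (q, a) = (10%, 50%), (20%, 60%) and (30%, 70%). The gain of 5 points is first confined to current smokers.

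**Formulas.**
- Baseline = (1 − q) × 0.16 + q × a
- Pooled effect d = (1 − q) × 0.05
- Sample-size ratio R = [p(1 − p) / 0.151] × (0.05 / d)², where p is the mean of the two pooled rates
- Power of a design that has exactly 80% for 16% versus 21%, two-sided 5% = Φ(2.80 / √R − 1.96)

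With the intracluster correlation and cluster autocorrelation held at their stated values, each variance component is proportional to p(1 − p). The ratio R therefore applies whatever the stepped-wedge layout.

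| | q = 10%, a = 50% | q = 20%, a = 60% | q = 30%, a = 70% |
|---|---|---|---|
| Baseline | 0.144 + 0.050 = 19.4% | 0.128 + 0.120 = 24.8% | 0.112 + 0.210 = 32.2% |
| Pooled effect | 4.5 points | 4.0 points | 3.5 points |
| p(1 − p) | 0.170 | 0.196 | 0.224 |
| R | 1.4 | 2.0 | 3.0 |
| Power | 66% | 50% | 36% |

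**Sensitivity to the assumptions.**
- If quitters also gain 5 points, d stays at 5 and only the variance changes. Power is 75%, 69% and 63%.
- If the gain in smokers equals the cited relative risk of 1.44, it is 16% × 0.44 = 7.04 points. Confined to smokers, the pooled effect is 6.3, 5.6 and 4.9 points, and power is 91%, 78% and 62%.

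**Case mix.** With no true effect, a change in q alone moves pooled abstinence by the change × (a − 0.16). A 10-point rise gives 3.4, 4.4 and 5.4 points. An apparent gain of 5 points would need a rise of 0.05 / (a − 0.16), which is 14.7, 11.4 or 9.3 points. This shows how sensitive the estimate is; it does not show that such a rise will happen.

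**The case against.** The strongest reply is that the mixed group is the intended population and the hypothesis is loosely worded. Eligibility, both outcome rows and the Discussion agree on it. The Sample size section never says current at booking, and its source count, "NSW Health data indicate there were over 2000 women smoking in the first half of pregnancy in the participating sites in 2018", can include women who stopped before booking. That supports the mixed group as one legitimate choice. It does not rescue the power basis, because the hypothesis ties the 16% to current smokers at booking.

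The size of the loss is also open to challenge. The share, the abstinence rate and the absence of benefit in quitters are all assumed. Verified abstinence requires interview consent, reported abstinence since birth and a saliva sample, and unverified women count as smokers, so the quitters' rate could be lower than assumed. The article calls its 5 points conservative and claims more than 80% power, so starting from exactly 80% is the least favourable reading. All of this stands and makes the figures illustrative.

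A reader might infer that case mix will mimic a treatment effect, because trained clinicians record status at booking. The article does not support that. A woman re-recorded from quit to smoker, or the reverse, stays in the mixed set with the same outcome, so the pooled rate does not move. Random step order, site effects and the time effect absorb stable site differences and common trends. Only a change within sites, around crossover, in which women enter the set could bias the estimate, and nothing in the article shows one.

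Nor does it follow that restricting to current smokers is the safer choice. That set depends more heavily on a status recorded after crossover by clinicians whom the intervention trains. The lack of a booking-status term in the listed model may be a detail left to the analysis plan, so it is not counted as an error.

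**Conclusion.** The contradiction holds and rests on the text alone: the article defines two incompatible primary populations and powers the trial on one while defining the primary outcome on the other. The 16%, the 21% and the power of more than 80% are not derived for the population in Table 2.

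The direction is a higher baseline, provided quitters do better than 16%, and a diluted effect, provided the gain is confined to smokers. The size cannot be fixed from the article. Under the assumed shares and rates, nominal 80% power becomes about 66% to 36%, with the smaller losses shown above if quitters benefit or the true effect is larger. A change of case mix at crossover is a possibility to check, not a demonstrated bias.

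**What to change.** Before analysis, state one primary population in the abstract, the Primary hypothesis, the eligibility criteria, the outcome rows of Table 2 and the Sample size section. The choice is the sponsor's:

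- **(a) Current smokers at booking.** Make them the primary analysis set, report recent quitters separately, and count only current smokers toward the 4320.
- **(b) The mixed set.** Keep both groups, amend the hypothesis to say so, and restate baseline, effect and power for that group, giving the assumed share of recent quitters and their assumed abstinence rate.

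Under either option, report results by booking status, and report the share of recent quitters before and after crossover at each site. Option (a) needs this check most, because its analysis set depends on the recorded status.

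The cost is wording and, for (b), a repeat of the power calculation. Option (a) leaves fewer women in the primary set for the same recruitment. Smoking status is already a required eMaternity field at the first visit, so no new data collection is needed.
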